##### Vaccination status—intention-to-treat

Intention-to-treat (ITT) vaccination is defined as an enrolled child receiving the allocated schedule but with administration outside the PP criteria. ITT administration of the standard schedule will require administration of three or four doses of PCV with the final dose <252 days (<36 weeks) of age. ITT administration of the alternative schedule will be defined as administration of two doses of PCV with administration of the first dose ≤182 days (≤26 weeks) of age and administration of the second dose ≥336 days (≥48 weeks) of age.

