### Adherence and protocol deviations

#### Definition and assessment of adherence to the intervention

##### Vaccination status—per-protocol

Vaccination per-protocol (PP) will be defined as a child enrolled into the study at ≤273 days (≤40 weeks) of age and who received the allocated schedule of PCV doses during follow-up. PP administration of the standard schedule of three doses will require allocation to the standard schedule and administration of three doses of PCV at ≤152 days (≤22 weeks) of age. PP administration of the alternative schedule will require administration of two doses of PCV, the first dose ≤152 days (≤22 weeks) of age, and administration of the second dose ≥273 days (≥40 weeks) and ≤365 days (≤52 weeks) of age.

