##### Vaccination status—incomplete vaccination

Incomplete vaccination with the standard schedule will be defined as administration of only one dose of PCV, or administration of two doses of PCV with the second dose administered at ≤252 days (≤36 weeks) of age. Incomplete vaccination with the alternative schedule will be defined as the administration of only one dose of PCV, at any age. For individual-level ITT analyses, children with incomplete vaccination will be assigned to the group to which they were randomised.

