##### Assessment of individual-level adherence

Individual-level adherence will be assessed as (a) PP vaccination, (b) ITT vaccination, (c) incomplete vaccination, (d) cross-over, (e) unvaccinated, or (f) migration/death before completion. Individual-level adherence will be assessed cumulatively over the 4 years of intervention and reported as proportions of participants enrolled at EPI clinics who fall into these mutually exclusive categories.

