##### Assessment of population-level adherence

Population-level adherence to the intervention, or the extent of exposure to the two schedules in the populations of the two groups, will be assessed according to eight mutually exclusive categories (Table 3). Population-level adherence will be assessed by group, on every day of the 4-year intervention period, with all resident children aged 0–260 weeks categorised on each day according to the eight categories. The age at which children are considered eligible refers to the earliest age at which children may have received doses of PCV, taking into account the predominant timing of EPI clinics once per month. That is, the first dose of PCV is scheduled to be given at 6 weeks of age, while the first opportunity to receive the first dose is when the monthly EPI clinic is held and an infant is aged 6 weeks or greater, which may be when the infant is 10 weeks of age. A dose of PCV administered before 6 weeks of age is considered ‘effective’ given the known immune response when PCV is administered in the neonatal period [22, 23].

**Table 3 Tab3:** Population-level adherence to the intervention for resident children aged 0–260 weeks

	Alternative schedule	Standard schedule
Ineligible 0 doses	Age <10 weeks and 0 doses	Age <10 weeks and 0 doses
Eligible 0 doses	Age ≥10 weeks and 0 doses	Age ≥10 weeks and 0 doses
Eligible 1 dose	Age <44 weeks and 1 dose	Age <14 weeks and 1 dose
Eligible 2 doses	Age ≥36 weeks and 2 doses and PCV2 ≥36 weeks	Age <18 weeks and 2 doses
Eligible 3 doses	3 doses and age PCV3 ≥36 weeks	3 doses and age PCV3 <36 weeks
Eligible 4 doses	Enrolled 2 Sept 2019–7 Feb 2020 and 4 doses and age PCV4 ≥36 weeks	4 doses and age PCV4 <36 weeks
Incomplete	Age ≥36 weeks and 1 dose Age <36 weeks and 2 doses Age ≥36 weeks and 2 doses and age PCV2 <36 weeks	Age ≥14 weeks and 1 dose Age ≥18 weeks and 2 doses
Cross-over	3 doses and age PCV3 <36 weeks 4 doses and age PCV4 <36 weeks	3 doses and age PCV3 ≥36 weeks 4 doses and age PCV4 ≥36 weeks

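### The adherence categories declared mutually exclusive overlap in places and leave some dose histories unclassified, and the per-protocol booster limit equates 273 days with 40 weeks

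*SAP article*

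**What the plan says.** **Individual level.** Under 'Assessment of individual-level adherence', six classes (PP, ITT, incomplete, cross-over, unvaccinated, migration/death) are to be "reported as proportions of participants enrolled at EPI clinics who fall into these mutually exclusive categories". For the alternative arm the preceding sections define them as follows:

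- PP: two doses, with dose 1 by day 152 and, for dose 2, "administration of the second dose ≥273 days (≥40 weeks) and ≤365 days (≤52 weeks) of age".
- ITT: "an enrolled child receiving the allocated schedule but with administration outside the PP criteria", then in figures two doses, the first by day 182 and "administration of the second dose ≥336 days (≥48 weeks) of age".
- Incomplete: "Incomplete vaccination with the alternative schedule will be defined as the administration of only one dose of PCV, at any age".
- Cross-over by doses: three or four doses, the last before day 252.
- Out-migration or death by day 294 (42 weeks): 'unvaccinated' with no dose, 'complete' with one dose.

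**Population level.** 'Assessment of population-level adherence' places every resident child, every day, in one of eight categories that it also calls mutually exclusive. In the alternative column of Table 3, 'Eligible 1 dose' is "Age <44 weeks and 1 dose" and 'Incomplete' includes "Age ≥36 weeks and 1 dose". The section on presenting adherence among resident children plots these categories as daily stacked bars to a 100% total.

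**Deviations.** Table 4 lists, for the alternative arm, a second or third dose before 40 weeks.

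**The concern.** A partition needs every child to fall in exactly one category. If the written rules put some children in two categories and others in none, the adherence table and daily plot cannot be produced from the SAP alone. Someone must then choose tie-breaks and a home for the unclassified children, after data have accrued in an unmasked trial.

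This matters more than usual in a non-inferiority trial. Readers use adherence to judge whether a finding of no difference could partly reflect arms that received similar schedules. The unclassified alternative-arm histories include two early doses, which is a direct departure from the allocated schedule.

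The PP definition also builds the PP cohort used for tertiary endpoints ('Individual-level cohorts') and the before-and-after-booster comparison ('Additional analyses'). An ambiguous day limit there reaches beyond description.

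**Working it through.** **1. Table 3, one dose, alternative arm.** 'Eligible 1 dose' runs to under 44 weeks and 'Incomplete' starts at 36 weeks.

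- Overlap: 44 − 36 = 8 weeks, or 8 × 7 = 56 days (days 252 to 307).
- Share of the 0–260 week range: 8/260 = 3.1%. This is a ceiling. It assumes uniform ages and that every alternative-arm child holds exactly one dose throughout the band.
- Floor for a PP child: dose 1 by day 152 and dose 2 no earlier than day 273 means exactly one dose on days 252–272, that is 272 − 252 + 1 = 21 days. Every PP child who passes through those ages during the trial meets both rows for at least 21 days.

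The same two-row check on the standard column of Table 3 finds no overlap and no gap.

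**2. Alternative-arm histories across the three schemes.**

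| Dose history | Individual-level class | Table 3 | Table 4 |
|---|---|---|---|
| Two doses, second before day 252 (e.g. days 60 and 110) | none | Incomplete | deviation |
| Two doses, second on days 252–272 | none | Eligible 2 doses once given | deviation |
| First on days 153–182, second on days 273–335 | meets no numeric limits | Eligible 2 doses once given | not listed, except days 273–279 if 40 weeks means 280 days |
| Three doses, third at day 252 or later | none | Eligible 3 doses | deviation if dose 2 or 3 is before 40 weeks |
| Four doses, fourth at day 252 or later | none | Eligible 4 doses only if enrolled 2 Sept 2019–7 Feb 2020; otherwise none | deviation if dose 2 or 3 is before 40 weeks |

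For the first two rows: PP needs dose 2 at day 273 or later, the ITT figures need day 336 or later, incomplete needs one dose, cross-over by doses needs three or four, and the out-migration/death class covers only zero or one dose. Nothing is left.

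**3. Labels and edges.**

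- An alternative-arm child with one dose who leaves or dies by 42 weeks is 'complete' in the out-migration/death section and 'incomplete' in the incomplete-vaccination section. The parallel standard-arm label for one or two doses says 'incomplete'.
- In the standard arm, two doses with the second on day 252 and an interval above 152 days is incomplete (day 252 or earlier) and also cross-over (day 252 or later). The clash is on that one day.

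**4. Days against weeks.**

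- 182/7 = 26, 252/7 = 36, 294/7 = 42 and 336/7 = 48 all match the printed weeks.
- 273/7 = 39.0 exactly, but 40 is printed; 40 × 7 = 280.
- Days 273–279 (7 days) are therefore PP by days, not PP by weeks, and a deviation if Table 4's 40 weeks means 280 days.
- The PP window for dose 2 is 365 − 273 + 1 = 93 days, so the disputed week is 7/93 = 7.5% of it. The SAP does not say what share of second doses falls in that week.

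**The case against.** **A reader might infer that PP and ITT overlap.** On the figures alone, dose 1 by day 152 with dose 2 on days 336–365 meets both sets of limits. The SAP does not support that reading. It defines the ITT class as "an enrolled child receiving the allocated schedule but with administration outside the PP criteria", so such a child is PP. This is not a defect.

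**The gap for dose 1 on days 153–182 with dose 2 on days 273–335 may be closed by the same wording.** The general definition could take in a child who is outside PP on timing alone. It does not sit with the stated figures, however, so the class needs clarifying.

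**Early second doses are not lost.** Table 4 reports them as deviations, and Table 3 classes them as incomplete when the second dose comes before 36 weeks. That is right, and it rules out any claim that the error disappears. What stands is that the individual-level table has no row for these children and so disagrees with the other two.

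**No main result moves.** The primary endpoint is analysed regardless of schedule or doses received, and the ITT cohort takes all enrolled children. The PP cohort depends only on the PP definition. The plot of growing exposure relies on the two-, three- and four-dose rows, which the one-dose overlap does not touch. All of this stands.

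**Forty weeks may simply be the SAP's label for 273 days**, since the PP section pairs them each time. If so, the conflict with Table 4 vanishes in intent. The PP definition as printed still carries two different limits.

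**The standard-arm clash is a single day.** It is trivial in size, but is corrected by the same edit.

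**Conclusion.** The point holds as a set of internal contradictions in the adherence definitions. The Table 3 overlap and the missing individual-level categories follow directly from the printed rules and need no outside assumption.

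The overlap covers at most about 3% of alternative-arm under-five time, given uniform ages and one dose held throughout the band. Within it, each PP child passing through those ages during the trial is doubly classified for 21 to 56 days. The number of unclassified children cannot be estimated from the SAP.

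It would go too far to say that adherence will be misreported, or that children awaiting the booster will be shown as incomplete. With no precedence rule they could equally be shown as 'Eligible 1 dose'. The supportable statement is that the table and the 100% bars cannot be produced as defined without a rule that the SAP does not contain.

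The effect is on adherence reporting and, through the 273-day/40-week mismatch, on the edge of the PP cohort. The primary and ITT analyses are unaffected. It should be corrected, but it does not threaten the trial's main conclusion.

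**What to change.** Reconcile the vaccination-status sections, Table 3 and the protocol-deviation definitions (including Table 4) into one ordered partition stated in days:

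- State the order in which categories are assigned, including where out-migration/death ranks against incomplete and unvaccinated.
- Give every dose history a category. This includes alternative-arm children with two doses and an early second dose, those with three or four doses and the last at day 252 or later, and those with a first dose on days 153–182.
- Make the two one-dose rows in the alternative column of Table 3 meet at a single age.
- Correct the 'complete' label for one-dose alternative-arm children who leave or die by 42 weeks, and let only one of the two standard-arm rules include day 252.
- Use the same day limits in the PP definition and Table 4, and drop week equivalents that do not match.

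The SAP does not settle which ages are intended, so the sponsor must choose them, preferably before anyone classifies the data by arm. The cost is SAP wording and a short classification program. Data collection does not change.

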##### Vaccination status—incomplete vaccination

Incomplete vaccination with the standard schedule will be defined as administration of only one dose of PCV, or administration of two doses of PCV with the second dose administered at ≤252 days (≤36 weeks) of age. Incomplete vaccination with the alternative schedule will be defined as the administration of only one dose of PCV, at any age. For individual-level ITT analyses, children with incomplete vaccination will be assigned to the group to which they were randomised.

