**Methods and design:**

PVS is a real-world field trial of an alternative schedule of one dose of PCV scheduled at age 6 weeks with a booster dose at age 9 months (i.e. the alternative ‘1+1’ schedule) compared to the standard schedule of three primary doses scheduled at 6, 10, and 14 weeks of age (i.e. the standard ‘3+0’ schedule). Delivery of the interventions began in late 2019 in 68 geographic clusters and will continue for 4 years. The primary endpoint is the prevalence of nasopharyngeal vaccine-type pneumococcal carriage in children aged 2–260 weeks with clinical pneumonia in year 4. Secondary endpoints are the prevalence of vaccine-type pneumococcal carriage among all ages in year 4 and the incidence of radiological pneumonia in children enrolled to receive the interventions. Additional disease and carriage endpoints are included.

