##### Vaccination status—out-migration or death before age to complete vaccination

Vaccination status in individual-level analyses will be defined as out-migration or death before age to complete if the child migrates out at an age before which their PCV schedule could reasonably be completed. Infants resident in standard schedule villages who out-migrate or die before age ≤112 days (16 weeks) and receive zero doses of PCV will be classified as ‘standard schedule, out-migration/death, unvaccinated before age 16 weeks’ and ‘standard schedule, out-migration/death, incomplete before age 16 weeks’ if one or two doses are received. Infants resident in alternative schedule villages who out-migrate or die before age ≤294 days (≤42 weeks) and receive zero doses of PCV will be classified as ‘alternative schedule, out-migration/death, unvaccinated before age 42 weeks’ and ‘alternative schedule, out-migration/death, complete before age 42 weeks’ if one dose of PCV is received.

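### Individual-level adherence has no category for infants still too young to complete when the 4 years end, so one-dose alternative-arm infants not yet due a booster count as incomplete

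*SAP article*

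**What the plan says.** Under 'Assessment of individual-level adherence' the SAP states: "Individual-level adherence will be assessed cumulatively over the 4 years of intervention and reported as proportions of participants enrolled at EPI clinics". The categories are mutually exclusive: "a) PP vaccination, (b) ITT vaccination, (c) incomplete vaccination, (d) cross-over, (e) unvaccinated, or (f) migration/death before completion".

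'Incomplete vaccination' is defined by number of doses, with no condition on the child's current age:
- Alternative arm: "Incomplete vaccination with the alternative schedule will be defined as the administration of only one dose of PCV, at any age".
- Standard arm: "administration of only one dose of PCV, or administration of two doses of PCV with the second dose administered at ≤252 days".

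The section on out-migration or death before age to complete vaccination is the only place where the individual-level scheme allows for a child too young to have finished. It applies "if the child migrates out at an age before which their PCV schedule could reasonably be completed", or if the child dies. The age limits are 42 weeks in the alternative arm ("Infants resident in alternative schedule villages who out-migrate or die before age ≤294 days (≤42 weeks) and receive zero doses of PCV") and 16 weeks in the standard arm ("Infants resident in standard schedule villages who out-migrate or die before age ≤112 days (16 weeks) and receive zero doses of PCV"). One-dose leavers in the alternative arm are labelled 'complete before age 42 weeks'. Leavers with one or two doses in the standard arm are labelled 'incomplete before age 16 weeks'.

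On timing, the abstract says: "Delivery of the interventions began in late 2019 in 68 geographic clusters and will continue for 4 years". The SAP gives no enrolment end date and no date to which doses are counted for adherence.

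**The concern.** An alternative-arm infant who is enrolled and given the first dose in the last months of the 4 years is on schedule but cannot yet have had the booster. That infant fits none of PP, ITT, cross-over or unvaccinated, and has neither migrated nor died. What remains is 'incomplete', and the words on age in that definition put the infant there explicitly. The same happens in the standard arm, but only for the few weeks between the first and third doses.

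The frequency table and stacked bars described under 'Presentation of adherence among participants enrolled to receive interventions' would then mix two groups: children whose booster was missed and children whose booster was not yet due. Under 'Background and rationale' the SAP makes booster timing and coverage part of its interpretation and plans modelling with varied booster coverage. A reader of that table could take part of the end-of-trial cut-off for failed booster delivery.

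**Working it through.** The SAP predicts no adherence proportion, so there is no stated figure to reproduce. The check estimates the share of enrolees cut off before completion.

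**Inputs from the SAP**
- Duration: 4 years = 4 × 365.25 / 7 = 208.7 weeks.
- Age by which completion is expected: 42 weeks (alternative) and 16 weeks (standard), the SAP's own limits. Ranges tried: 39-44 and 14-18 weeks.
- Age at enrolment and first dose: 6-10 weeks, midpoint 8. The first dose is scheduled at 6 weeks and, with monthly clinics, may come at 10.

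**Assumptions (not in the SAP)**
- Uniform enrolment to the last day, and no doses counted after it.
- Older infants enrolled at start-up (allowed up to 9 months in the alternative arm; under 6 months or third dose not yet received in the standard arm) add S weeks of births to the denominator: 28-33 (central 31) in the alternative arm and about 18 in the standard arm. S = 0 is also shown.
- 80-95% of cut-off infants would otherwise have completed.

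**Share cut off** = (completion age − enrolment age) / (208.7 + S)

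| Arm | Central, S = 0 | Central, with start-up | Range |
|---|---|---|---|
| Alternative | (42 − 8)/208.7 = 16.3% | 34/239.7 = 14.2% | (39 − 10)/241.7 = 12.0% to (44 − 6)/208.7 = 18.2% |
| Standard | (16 − 8)/208.7 = 3.8% | 8/226.7 = 3.5% | (14 − 10)/208.7 = 1.9% to (18 − 6)/208.7 = 5.7% (S = 0) |

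A simulation of 2 million births with monthly clinics gave 16.0% (S = 0) and 13.8% (with start-up) in the alternative arm, and 4.2% and 3.9% in the standard arm.

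**Points of adherence lost** = share × proportion who would have completed
- Alternative, completion at 40-42 weeks and enrolment at 8: 0.80 × 32/239.7 = 10.7 to 0.95 × 34/208.7 = 15.5 points.
- Standard, completion at 14-18 weeks and enrolment at 8: 0.80 × 6/226.7 = 2.1 to 0.95 × 10/208.7 = 4.6 points.
- Difference between arms at the central ages, with equal completion: 0.80 × (14.2 − 3.5) = 8.6 to 0.95 × (16.3 − 3.8) = 11.9 points.

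**Sensitivity to a lag g (weeks) between close of enrolment and the adherence cut.** Alternative-arm share = (34 − g)/(208.7 − g + S); standard-arm share = (8 − g)/(208.7 − g + 18), floored at 0.

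| g | Alternative (S = 31 to S = 0) | Standard |
|---|---|---|
| 0 | 14.2-16.3% | 3.5% |
| 4.3 | 12.6-14.5% | 1.7% |
| 8.7 | 11.0-12.6% | 0% |
| 13 | 9.3-10.7% | 0% |
| 26 | 3.7-4.4% | 0% |
| 34 | 0% | 0% |

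Counting boosters given after the 4 years has the same effect as a longer lag.

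**The case against.** The strongest objection is that the size rests on two facts the SAP does not give: when enrolment closes and when dose counting stops. The PP definition credits doses received during follow-up, and surveillance may outlast delivery. Four years from the first dose (2 September 2019), or from the first day of full opportunity to enrol (7 October 2019), end before twelve months of year 4 surveillance starting on 1 November 2022. That surveillance may be extended by 1-2 months. If doses were counted to the end of surveillance, the lag would be roughly 4 to 17 weeks, between the 4.3- and 26-week rows above. This stands: the size must be given as a range, and a share above 10% is not assured. It does not remove the fault, because the classification rule is written and the SAP ties the adherence assessment to the 4 years of intervention.

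It is also fair that the consequence is confined to a descriptive display. Table 3 already conditions population-level adherence on current age: an alternative-arm child with one dose counts as eligible, unambiguously so below 36 weeks. The primary endpoint and the ITT cohorts include children regardless of doses received. A one-dose infant is outside the alternative-arm PP definition under either label. All of this stands.

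The label 'complete before age 42 weeks' can be read as complete for age, since such a leaver may have had every dose due and sits in the separate category (f). It is therefore not a proven contradiction. It does use the opposite word from the standard-arm label and from the definition of incomplete, so the wording needs reconciling.

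**Conclusion.** The point holds for the individual-level adherence scheme. Infants still resident and alive but too young to complete at the end of the period have no category of their own, and the stated definition places one-dose alternative-arm infants in 'incomplete'. With uniform enrolment to the end of year 4 and no later doses counted, about 12-18% of alternative-arm enrolees are affected (about 11-16 points of adherence) against about 2-6% in the standard arm. This falls to about 9-11% against 0% with a 13-week lag, and to about 0% with a lag of about 34 weeks or if later boosters are counted.

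A reader might infer three stronger things that the SAP does not support:
- That the fault lies in one arm only. The standard arm is affected too, to a smaller degree.
- That any reported adherence gap would be largely an artefact. The SAP predicts no gap, so the share due to cut-off is unknown.
- That trial results are biased. No effect estimate depends on this classification, and Table 3 is unaffected.

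It is worth correcting before the final analysis because the misclassification is unequal between arms and the correction is simple.

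**What to change.** 1. Under 'Assessment of individual-level adherence' and the section on leaving or dying before age to complete, add end of the intervention period before age to complete to category (f), with the existing 42- and 16-week limits.
2. Under 'Vaccination status—incomplete vaccination', restrict the category to children followed past those ages.
3. State the date to which doses are counted for individual-level adherence.
4. Reconcile the label for one-dose alternative-arm leavers with the definition of incomplete vaccination and with the parallel standard-arm label.

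Optionally, add a second table limited to children past 52 weeks (alternative) and 22 weeks (standard) at the cut, the upper ages in the PP definition. Its denominator would be somewhat smaller.

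The cost is a few lines of SAP text and one derived variable from dates already held. No new data are needed and no effect analysis changes.
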